#### Definition of the dosage

For arm A, the total dose for CTV should be 65.6GyE in 16 fractions (4.1GyE per fraction) in 4 weeks. For arm B, the total dose for CTV should also be 65.6GyE in 16 fractions (4.1GyE per fraction) and CTV boost be 72GyE in 16 fractions (4.5GyE per fraction) simultaneously. Moreover, 95% of the prescription dose should cover 100% of the CTV and 90% of the prescription dose should cover 100% of the PTV in both arms. The dose constraints of organs at risk are defined as rectum Dmax ≤ 100%PD, V60 ≤ 3cc, V55 ≤ 7cc, V50 ≤ 10cc and V30 ≤ 15cc, bladder Dmax ≤ 100%PD, D15% ≤ 40GyE, and D5% ≤ 50GyE.

### Duration of the study

The primary endpoint is to compare the treatment-induced grade 2 or greater acute toxicity between arm A and arm B. Seventy patients are planned to be enrolled in each arm, and 140 patients are enrolled in total.

It will take about 5 years to complete the enrollment of all patients and every patient should complete at least 3 months of follow-up work after radiotherapy. The study is expected to start in October 2020 and primarily be completed in July 2025.

### Outcome measures

The primary objective of this phase II randomized study is to evaluate the differences of acute toxicities in patients with localized prostate cancer treated with carbon ion radiotherapy and SIB carbon ion radiotherapy.

Late toxicities, biochemical relapse-free survival, overall survival, and progression-free survival are the secondary outcome measures to preliminarily explore the optimal dose and efficacy of SIB carbon ion radiotherapy of localized prostate cancer.

Additionally, 25ml of peripheral blood and 35ml of urine will be collected prospectively before and after treatment for the detection of immune and circulating tumor cells related to prostate cancer carbon ion therapy. The purpose of these indicators’ detection is to evaluate the efficacy and toxicity of prostate cancer carbon ion therapy and then to predict the prognosis of the disease. Before the collection of biological specimens, an informed consent form will be provided by the principal investigator to patients.

Moreover, EQ-5D, IPSS, and EPIC questionnaires are used to evaluate the effect of carbon ion radiotherapy on patients’ quality of life. IPSS would be used to assess the lower urinary tract symptoms. EPIC would be used to evaluate the urinary, bowel, and sexual symptoms.

### Evaluation of side effects

Acute toxicities from treatment are graded according to NCI-CTCAE version 4.03 [37]. Late toxicities from treatment are graded according to Radiation Therapy Oncology Group/European Organization for Research and Treatment of Cancer (RTOG/EORTC) criteria [38]. Late toxicities are defined as symptoms first occurring or lasting > 90 days from radiotherapy.

### Criteria for discontinuation

Patients should be discontinued from the study if any of the following conditions occur:Occurrence of treatment-related serious adverse events.Patients’ requirement to withdraw from the study.Disease progression.Serious breach of the research protocol.Death of the subject.The investigator considers that the patient should be discontinued from the study.

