During irradiation, all patients are regularly assessed for acute toxicities of normal tissues at least once a week until they have subsided. The adverse events, grading, and correlation with radiotherapy are documented at each evaluation. Specific evaluation contents include weekly routine blood tests to observe the hematological toxicity, monthly liver function tests to observe the liver toxicity, weekly routine urine examination to observe the occurrence of hematuria and urinary tract infection, IPSS questionnaire to evaluate urinary system toxicity, and weekly routine stool examinations and occult blood examinations combined with the symptoms of intestinal toxicity to exclude radioactive enteritis. Patients are treated with combined endocrine therapy, either neoadjuvant endocrine therapy or concurrent endocrine therapy, depending on their grading. When necessary, a supportive medication is initiated or adapted. When patients experience treatment-related adverse events, appropriate medications will be given according to the severity of the disease. If patients have an unexpected injury during the clinical study, financial compensation will be made in accordance with Chinese laws and regulations. Additionally, quality of life is collected during and at the end of radiotherapy. Table 1 summarizes the schedule.

**Table 1 Tab1:** Schedule of the trial

	Before radiation	During radiation	At the end of radiation (the final day of radiation)	Follow-up after treatment						
		Every week		The first year				The second and third years	The fourth year	From the fifth year
				Weeks 4–6 (first time)	The 3rd month	The 6th month	The 12th month	Every 3 months	Every 6 months	Every year
**Written informed consent**	**√**									
**Medical history/physical examination**	**√**	**√**	**√**	**√**	**√**	**√**	**√**	**√**	**√**	**√**
**KPS, ECOG**	**√**	**√**	**√**	**√**	**√**	**√**	**√**	**√**	**√**	**√**
**Pathological diagnosis**	**√**									
**Inclusion and exclusion criteria**	**√**									
**Peripheral blood routine examination**	**√**	**√**^**a**^	**√**	**√**	**√**	**√**	**√**	**√**	**√**	**√**
**Serum chemistry**	**√**	**√**^**a**^	**√**	**√**	**√**	**√**	**√**	**√**	**√**	**√**
**Urine and stool routine examination**	**√**	**√**^**a**^	**√**	**√**^**a**^	**√**^**a**^	**√**^**a**^	**√**^**a**^	**√**^**a**^	**√**^**a**^	**√**^**a**^
**Levels of PSA, fPSA, testosterone, and NSE**	**√**		**√**	**√**	**√**	**√**	**√**	**√**	**√**	**√**

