**Tests for HIV, syphilis**	**√**									
**Tests for HBV, HCV**	**√**									
**Cardiac function examination**	**√**									
**CT of the chest**	**√**						**√**	**Annually**	**Annually**	**Annually**
**CT scan or ultrasound of the abdomen**	**√**		**√**	**√**	**√**	**√**	**√**	**√**	**√**	**√**
**mpMRI of prostate**	**√**		**√**	**√**	**√**	**√**	**√**	**Annually**	**Annually**	**Annually**
**Bone scan examination**	**√**^**a**^						**√**	**Annually**	**Annually**	**Annually**
**68Ga-PSMA PET/CT**	**√**^**b**^		**√**^**b**^				**√**	**Annually**	**Annually**	**Annually**
**Evaluation of acute toxicities (NCI-CTACE)**	**√**	**√**	**√**	**√**	**√**			**√**		
**Evaluation of late toxicities (RTOG/ EORTC)**					**√**	**√**	**√**	**√**	**√**	**√**
**EPIC**	**√**	**√**	**√**		**√**	**√**	**√**	**Annually**	**Annually**	**Annually**
**EQ-5D**	**√**	**√**	**√**		**√**	**√**	**√**	**Annually**	**Annually**	**Annually**
**IPSS**	**√**	**√**	**√**		**√**	**√**	**√**	**Annually**	**Annually**	**Annually**

^a^when necessary

^b^recommended

All the patients will be followed up according to the protocol every 3 months in the initial 3 years after the completion of treatment, every 6 months for an additional year, and every year thereafter. Follow-up examinations include complete history, physical examination, digital rectal examination, PSA, complete blood count, serum chemistry, CT of the chest, CT scan or ultrasound of the abdomen, mpMRI of the prostate, bone scan examination, and 68Ga-PSMA PET/CT which will be performed earlier if recurrence is suspected. Every patient is recommended to evaluate PSA at the same laboratory. In addition, quality of life should be assessed regularly during follow-up.

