### Plans to promote participant retention and complete follow-up

The subjects will be recruited once they are hospitalized and they will remain in the site until discharge. Patients have the right to withdraw during the study, which will not affect the subsequent medical treatment. If the subject withdraws, the investigator must record the reason and date of withdrawal on the subject’s case report form (CRF). All subjects who withdrew due to adverse events or abnormal laboratory test results must be followed up until they recover or stabilize, and subsequent outcomes recorded. If patients develop disease progression, they should be followed up until death. If patients fail to receive all treatment regimens for any reason other than disease progression, follow-up including efficacy, toxicity, and quality of life should still be performed.

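### The discontinuation rule takes patients out of the study rather than off treatment, and for those who have completed all 16 fractions the retention section does not fully restore scheduled follow-up

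*Protocol article*

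**What the plan says.** Four places in the protocol article bear on this.

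- **Criteria for discontinuation.** "Patients should be discontinued from the study if any of the following conditions occur:Occurrence of treatment-related serious adverse events". The list goes on to the patient's own request, progression, serious breach of the protocol, death, and a discretionary item: "The investigator considers that the patient should be discontinued from the study". The object of discontinuation is the study; treatment is not mentioned.
- **Patient assessments (text after Table 1, and Table 1).** "All the patients will be followed up according to the protocol every 3 months in the initial 3 years after the completion of treatment", then half-yearly for a year, then yearly. The text adds that "quality of life should be assessed regularly during follow-up". Table 1 carries the rows "Evaluation of late toxicities (RTOG/ EORTC" and "Levels of PSA, fPSA, testosterone, and NSE" through all follow-up columns from month 3 onwards.
- **Duration of the study.** "every patient should complete at least 3 months of follow-up work after radiotherapy".
- **Plans to promote participant retention and complete follow-up.** Patients who withdrew because of adverse events or abnormal laboratory results "must be followed up until they recover or stabilize, and subsequent outcomes recorded". Patients with progression are followed until death. Patients who did not receive the whole treatment, for any reason except progression, still have efficacy, toxicity and quality-of-life follow-up.

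Statistical analysis plans an intention-to-treat analysis as randomised, with last observation carried forward or multiple imputation if data are missing.

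**The concern.** Stopping treatment and stopping observation are different acts, and the discontinuation rule does not separate them. Treatment takes four weeks (Definition of the dosage), whereas Table 1 runs to year 5 and beyond. Many triggering events can therefore occur when there is no treatment left to stop. For such a patient the literal rule ends participation while the follow-up text says to continue.

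What is at stake is the secondary data: late toxicity, PSA-based outcomes and quality of life. Late toxicity covers symptoms that first appear or persist more than 90 days after radiotherapy (Evaluation of side effects). If observation stops once one serious event has settled, a later new toxicity in the same patient may go unrecorded. The loss would depend on toxicity, in a trial that asks whether a boost adds toxicity, so it could differ by arm. The trial is open-label, so removal by investigator judgement could differ by arm as well. The two missing-data methods would not reliably repair this. Carrying the last value forward would carry the recovered or stabilised grade, and standard multiple imputation assumes data missing at random.

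**Working it through.** The plan gives no figure on this point, so the check sets the clauses side by side and then counts the visits in dispute.

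**Step 1. Which clause of the retention section covers whom?**

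- *Any non-progression trigger before the last fraction.* Treatment is incomplete, so the full follow-up clause applies. Resolved.
- *Progression, at any time.* Followed until death. Resolved.
- *Treatment-related serious event after all 16 fractions.* The incomplete-treatment clause cannot apply. The adverse-event clause applies, but it fixes only recovery or stabilisation as an end point. The further recording of outcomes has no stated schedule, duration or endpoints. Partly resolved.
- *Serious breach or investigator judgement after all 16 fractions.* No clause applies. The only texts left are the removal rule and the all-patient schedule, which point in opposite directions. Not resolved.

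**Step 2. How many scheduled visits are in dispute per affected patient?** The month-3 visit is left out, because Duration of the study asks for three months of follow-up for every patient. From Table 1, after month 3 through year 4:

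- Late toxicity: months 6 and 12 (2) + every 3 months in years 2 and 3 (8) + every 6 months in year 4 (2) = 12.
- PSA: same columns, 2 + 8 + 2 = 12.
- EPIC, EQ-5D and IPSS: months 6 and 12 (2) + annually in years 2, 3 and 4 (3) = 5.

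These counts assume removal soon after month 3 and are cut off at year 4. Table 1 continues yearly from year 5. The text after Table 1, with visits every 3 months from the start, would add a month-9 visit for late toxicity and PSA: 3 + 8 + 2 = 13.

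**Step 3. What share of an arm is one patient?** With 70 per arm, 1/70 = 1.4%. The document gives no rate of treatment-related serious events, breaches or investigator-judged removals, and none is assumed here, so the number of affected patients cannot be computed.

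**The case against.** The strongest reply is that the article's own usage counts against the literal reading. Progression and serious adverse events are both triggers, yet the section immediately following orders follow-up until death for the one and continued recording for the other. Discontinuation therefore does not seem to mean that data collection ends. Death and patient withdrawal also stop treatment, so their presence in the list does not prove that the rule reaches beyond treatment. The article condenses a fuller protocol that is not shown, and the follow-up text already says all patients.

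Much of this stands. It shows that the likely intention is to keep collecting data, and it confines the problem to patients who completed treatment. It does not remove the problem. The rule is printed in terms of the study, and the full-follow-up clause is conditional on incomplete treatment. A site that follows the text after a post-treatment serious event could stop at recovery. Two printed rules that pull apart are not the kind of detail an article simply leaves to its parent protocol.

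Three stronger readings are tempting, and the document does not support them:

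- *That nothing says which rule prevails.* The retention section does say so for incomplete treatment and for progression, and in part for adverse-event withdrawals.
- *That the rule contradicts the intention-to-treat plan.* Discontinuation does not take a patient out of an as-randomised analysis set. The patient stays in it with missing data, for which the plan names methods.
- *That the primary comparison is compromised.* A serious event that triggers removal will usually have been recorded already, and nothing provides for excluding such patients from the acute-toxicity analysis.

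**Conclusion.** The point holds as a minor inconsistency with a specific gap. For patients who completed all 16 fractions, the discontinuation rule and the follow-up schedule disagree. The retention section settles this only partly after a serious event, and not at all after a breach or an investigator's decision. Followed literally, up to 12 late-toxicity, 12 PSA and 5 quality-of-life visits per affected patient could be lost through year 4 on the Table 1 count.

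The total effect cannot be sized from the document, and a difference between arms is a possibility rather than something shown. The endpoints concerned are secondary and serve preliminary exploration of dose and efficacy (Outcome measures). The conclusion rests on reading the discontinuation wording literally. If sites already treat it as stopping treatment only, no data are lost and only the wording is at fault.

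**What to change.** - In Criteria for discontinuation, change the object from the study to *protocol treatment*, leave the clinical triggers as the sponsor decides, and cross-refer to the retention section.
- In the retention section, state that only death or withdrawal of consent for data collection ends follow-up.
- State that all other randomised patients stay on the Table 1 schedule in their assigned arm. Name those with a serious event after the last fraction, a protocol breach or an investigator-judged discontinuation.

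The cost is amendment wording, submitted through the route in Protocol amendments. No visit is added beyond those already scheduled.

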### Plans to promote participant retention and complete follow-up

The subjects will be recruited once they are hospitalized and they will remain in the site until discharge. Patients have the right to withdraw during the study, which will not affect the subsequent medical treatment. If the subject withdraws, the investigator must record the reason and date of withdrawal on the subject’s case report form (CRF). All subjects who withdrew due to adverse events or abnormal laboratory test results must be followed up until they recover or stabilize, and subsequent outcomes recorded. If patients develop disease progression, they should be followed up until death. If patients fail to receive all treatment regimens for any reason other than disease progression, follow-up including efficacy, toxicity, and quality of life should still be performed.

### Data monitoring/auditing

The study investigators will monitor the integrity of study data and participant safety. During the period of recruitment, regular analyses will be provided to the Institutional Review Board, who will give advice on the study conduction, protocol modification, and trial halt if needed.

Interim analyses were performed in order to assess the safety and efficacy of treatment. If a significant lack of efficacy or an unacceptable risk-benefit balance is found, the Institutional Review Board will organize an expert group to review this situation and make the final decision to terminate the trial.

The trial will be regularly audited on-site and online by experts, independent from investigators.

### Protocol amendments

Any important modifications to the protocol, such as changes to eligibility criteria, outcomes, and analyses will require a formal amendment to the protocol. Such amendment must be submitted to the Institutional Review Board for approval before implementation.

### Statistical analysis

The primary endpoint of the study is to observe the difference in acute toxicity in patients with localized prostate cancer who receive carbon ion radiotherapy and SIB carbon ion radiotherapy. All the patients will be randomly assigned to arm A and arm B in a ratio of 1:1. Assuming a type I error of 0.025 and type II error of 0.2, and under the assumption that the probability of no more than 2 degrees of acute GU and GI toxicities in arm A is 90% (Pc), and the probability of no more than 2 degrees of acute GU and GI toxicities in arm B is also 90% (Pt), with a non-inferiority margin of 0.15, we estimate that a sample size of 63 participants per arm will yield 80% power to show non-inferiority. However, anticipating a possible 10% dropout rate in each group, per arm *n* = 70 patients will be recruited into the study such that a total of *N* = 140 patients is required.

Statistical analysis will be performed using SPSS software (V20.0, SPSS Inc., Chicago, IL, USA). The Mann-Whitney *U* test will be used to compare the differences in acute and late toxicity between the two arms. The Kaplan-Meier method will be used to estimate the biochemical relapse-free survival, progression-free survival, and overall survival of the entire cohort. The association between each of the candidate prognostic factors with biochemical relapse-free survival, progression-free survival, and overall survival rates will be tested using the log-rank test. Multivariate analysis will be performed using the Cox regression model.

Analysis is planned on an intention-to-treat population (ITT), with all participants to be analyzed in the group to which they were randomized. We will make efforts to collect complete data for all participants and minimize missing data. If required, the missing data will be dealt with last observation carried forward method or multiple imputation.

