Currently, localized prostate cancer is mainly irradiated with conventional photon beam. Although intensity-modulated radiation therapy (IMRT)/image-guided radiation therapy (IGRT) could get better dose conformity than 3-dimensional conformal radiation therapy (3DCRT), the irradiation dose was still limited due to the surrounding dose-limiting structures such as rectum and bladder; otherwise, it might lead to severe gastrointestinal (GI) and genitourinary (GU) toxicities, which affect the patients’ quality of life. In addition, from the perspective of fractionation dose, conventional fractionated radiotherapy of prostate cancer might not achieve the best therapeutic effect [3–5]. Actually, although long-term results of the M. D. Anderson randomized trial [1] demonstrated that dose-escalation of conventional photon radiotherapy did improve freedom from biochemical and clinical progression, the 10-year incidence of grade 2 or greater GI toxicity was higher in the high-dose arm than in the low-dose arm (26% vs 13%, *p* = 0.013), as was the incidence of grade 2 or greater GU toxicity (13% vs 8%). Similarly, despite improved clinical or biochemical failure-free survival in the Dutch Phase III trial [6], the 7-year rate of late grade 2 or greater GI toxicity was 35% in the 78Gy arm versus 25% in the 68Gy arm (*p* = 0.04). A meta-analysis [7] showed that high-dose radiotherapy (74–80 Gy) was associated with an increased risk (odds ratio 1.72) of late grade 2 or higher GI toxicity compared with conventional-dose radiotherapy (64–70.2 Gy). Consequently, a better radiotherapy strategy is eagerly wanted.

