## Methods/design

### Trial organization/coordination

This study is designed as an open-label, prospective, single-center, randomized two-armed (carbon ion radiotherapy vs. simultaneous integrated boost radiotherapy) study, primarily evaluating the differences in the severity and incidence of acute toxicity in patients with localized prostate cancer treated with carbon ion radiotherapy and simultaneous integrated boost carbon ion radiotherapy and further optimizing carbon ion therapy for prostate cancer. The rationale for this SIB approach is to provide a greater overall tumor-killing effect to prolong the biochemical recurrence-free survival without additional toxicity as compared with standard treatment. The two study arms are defined by different treatment strategy with arm A (carbon ion radiotherapy at 65.6 Gy in 16 fractions) and arm B (SIB carbon ion radiotherapy to the imaging-visible malignancy at 72Gy in 16 fractions). The flow chart of this phase II trial is illustrated in Fig. 1. The study carries out in Shanghai Proton and Heavy Ion Center (SPHIC) in China, and ethical consent was obtained from the ethics committee of SPHIC before trial initiation. The number of the ethics committee of SPHIC (Institutional Review Board) is 2006-62-03. All patients have written informed consent before inclusion in the trial.

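### A pass against the 0.15 margin excludes only a toxicity excess of 15 points or more, so it cannot show that the boost adds no toxicity, and the named test does not address the margin

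*Protocol article*

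**What the plan says.** All of the following is in the protocol article.

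- **Design assumptions (Statistical analysis).** The error rates are given as "Assuming a type I error of 0.025 and type II error of 0.2". The probability of staying within the toxicity limit is 90% in arm A, and for arm B the text reads "the probability of no more than 2 degrees of acute GU and GI toxicities in arm B is also 90% (Pt". The trial is sized "with a non-inferiority margin of 0.15, we estimate that a sample size of 63 participants per arm will yield 80% power", and 10% dropout takes this to 70 per arm, 140 in all.
- **Test (same section).** The only method named for comparing acute toxicity between arms is the Mann-Whitney U test. No decision rule ties a result to the 0.15 margin.
- **Aim (Trial organization/coordination).** The rationale for the boost is longer biochemical recurrence-free survival "without additional toxicity as compared with standard treatment".
- **Context (Background).** Two photon dose-escalation trials are cited for late gastrointestinal toxicity of grade 2 or greater: 26% against 13% in one, and in the other "the 7-year rate of late grade 2 or greater GI toxicity was 35% in the 78Gy arm versus 25% in the 68Gy arm".

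**The concern.** The margin is one and a half times the whole event rate assumed for arm A. A design that tolerates any true excess below 15 points can answer whether the boost is much more toxic. It cannot answer whether the boost adds toxicity, which is how the rationale is worded. If a pass were reported in the words of that rationale, a moderate increase in acute toxicity, such as half as many events again, could go out under a statement that there was none.

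The second difficulty is that the sample size belongs to a non-inferiority comparison but the named test does not. The Mann-Whitney U test takes no difference between arms as its null hypothesis. A non-significant result is not evidence that the excess is below 15 points, and a significant one does not show that it is above. As written, the analysis never uses the margin that set the sample size.

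**Working it through.** **Inputs (Statistical analysis).** Event-free probability 0.90 in both arms, so event rate 0.10; margin 0.15; type I error 0.025, taken as one-sided; power 80%; 1:1 allocation; 10% dropout.

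**1. Reproduce the sample size.**
n = (1.96 + 0.8416)² × (0.9 × 0.1 + 0.9 × 0.1) / 0.15² = 62.8, so 63 per arm; 63 / 0.9 = 70.
This matches the article. One-sided 0.05 would give 50 and one-sided 0.0125 would give 77, so the margin is an absolute risk difference at one-sided 0.025.

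**2. What the margin tolerates.** The boundary for the true arm B rate is 0.10 + 0.15 = 0.25. The risk ratio there is 0.25 / 0.10 = 2.5, and the odds ratio is (0.25 / 0.75) / (0.10 / 0.90) = 3.0.

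**3. How often a true increase would pass.** The article gives no rule, so assume the usual one: pass if the upper limit of the two-sided 95% confidence interval for B minus A is below 0.15. The probability of passing is the sum of Bin(a; n, pA) × Bin(b; n, pB) over all outcome pairs (a, b) that pass. Arm A is truly 10%. Each range runs from the Newcombe to the Wald interval.

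| True arm B rate | 63 per arm | 70 per arm |
|---|---|---|
| 10% | 77–81% | 80–84% |
| 15% | 38–42% | 41–45% |
| 20% | 12–14% | 13–14% |
| 25% | under 3% | under 3% |

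Hand check by normal approximation, n = 63:
- At 15%: SE = √[(0.09 + 0.1275) / 63] = 0.0588; (0.15 − 0.05) / 0.0588 − 1.96 = −0.26, probability about 40%.
- At 20%: SE = √[(0.09 + 0.16) / 63] = 0.0630; (0.15 − 0.10) / 0.0630 − 1.96 = −1.17, probability about 12%.

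**4. What an observed pass looks like (Wald).** With 6/63 events in arm A (9.5%), arm B may have at most 8/63 (12.7%): difference 0.032, SE 0.056, upper limit 0.141. A ninth event gives 0.160 and fails. With 7/70 in arm A the most arm B may have is 9/70 (12.9%).

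**5. Excesses of the size cited in the Background.** Under the same rule, 13% against 26% passes about 5% of the time and 25% against 35% about 9–10%.

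**The case against.** The other side has several good points.

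- **A reader might infer that arm B could show 25% toxicity and still be called non-inferior.** It could not. The 25% is the boundary for the true rate; a true 25% passes less than 3% of the time, and the observed excess must stay near 3 points (step 4).
- **A reader might infer that the harms cited in the Background would usually slip through.** They lie inside the margin by definition, but excesses of 10 or 13 points pass only about 5–14% of the time across the base rates considered (10%, 13% and 25%).
- **A reader might take 10 points from the Background as the right margin.** The documents do not support this. Those figures are late toxicity after photon treatment. The primary endpoint is acute toxicity, graded on a different scale (CTCAE, against RTOG/EORTC for late effects), and late toxicity is a separate secondary endpoint. A 10-point criterion would also have only about 43–53% power at equal 10% rates with 63 to 70 per arm.
- **A reader might fault the absence of a reason for 0.15.** This is a condensed article, and the reason may be in the full protocol. A wide margin can also be a fair compromise in phase II.
- **The toxicity phrase is part of a rationale, not a rule for conclusions.** The Discussion speaks only of preliminary exploration, and no passage says that a pass will be reported as no added toxicity.

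All of this limits the point but does not remove it. A true rise by half would still pass about two times in five, the wording of the aim is stronger than the criterion can bear, and the named test leaves the margin unused. A rationale for 0.15 elsewhere would not change any of these.

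**Conclusion.** The point holds in limited form. The sample size is correct for its inputs. Meeting the 0.15 criterion would show that the true excess is below 15 points, that is, an arm B rate below 25% if arm A is 10%. It would not show that the boost adds no toxicity: a true 15% against 10% passes about 38–45% of the time, and a true 20% about 12–14%. The Mann-Whitney U test cannot deliver even the weaker conclusion.

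This rests on three assumptions: a true arm A rate of 10%; a pass judged by the upper 95% limit of the risk difference, which the article does not state; and 63 to 70 analysed patients per arm. The event behind the 10% also needs reconciling. The sample-size text counts toxicity up to and including degree 2 as acceptable, while the primary endpoint is grade 2 and higher. The arithmetic is the same for whichever event was meant.

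The documents do not support calling 0.15 wrong in itself, or replacing it with a figure taken from late photon toxicity. The issue should be corrected because it changes what the trial may conclude, not whether it can run.

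**What to change.** Keep 140 patients and the 0.15 margin.

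1. In Statistical analysis, make the primary toxicity comparison the risk difference (arm B minus arm A) with its two-sided 95% confidence interval. Declare non-inferiority only if the upper limit is below 0.15. Name the interval method, since the pass rates at 10% against 15% differ by about 4 points between Newcombe and Wald (42% against 38% with 63 per arm). The Mann-Whitney U test may stay as a supportive comparison of grades.
2. In the same section, state that a pass shows only that the excess of the primary toxicity event is below 15 percentage points, and that it will not be reported as no added toxicity.
3. In Trial organization/coordination, bring the wording of the rationale into line with that statement.

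**Cost.** There are no extra patients, visits or procedures. The Protocol amendments section requires a formal amendment and Institutional Review Board approval for a change to the analyses. It should be in place before toxicity is compared between arms for the primary analysis. The real price is a weaker headline claim.
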